# Mother And late Preterm Lactation Study (MAPLeS): a randomised controlled trial testing the use of a breastfeeding meditation by mothers of late preterm infants on maternal psychological state, breast milk composition and volume, and infant behaviour and growth

**DOI:** 10.1186/s13063-020-4225-3

**Published:** 2020-04-07

**Keywords:** Preterm infants, Late preterm infants, Breastfeeding, Breast milk, Maternal stress, Infant growth, Infant behaviour, Meditation, Relaxation therapy, Oxytocin

## Abstract

**Background:**

Late preterm infants suffer from more complications and are less likely to be breastfed compared to term infants and their mothers experience higher levels of stress than mothers with term infants. The physiological or hormonal responses that influence milk ejection, milk production, and/or maternal behaviour are possible mechanisms by which maternal distress could negatively influence breastfeeding success. Maternal mood might also affect infant behaviour (feeding, sleeping, and crying) through changes in milk volume and composition, and consequently breastfeeding success and infant growth. Previous research, using relaxation therapy in 64 Malaysian first-time mothers breastfeeding their full-term infants, demonstrated that the therapy was effective in reducing maternal stress and improving infant growth. We hypothesise that expected benefits are even greater in a more vulnerable population where additional breastfeeding support is especially needed, such as in mothers of late preterm infants.

**Methods/design:**

This protocol describes our randomised controlled trial that tests whether a breastfeeding meditation audio reduces maternal stress in mothers of late preterm infants in London. Home visits will be conducted at 2–3 and 6–8 weeks post-delivery. Participants will be randomised to a control group or an intervention group, where mothers will be asked to listen to a meditation tape on a daily basis while breastfeeding. The main outcomes of the intervention will be maternal stress markers and infant weight Z-score. Potential mediators will be the secondary outcomes and include breast milk macronutrient and hormone levels (ghrelin, leptin, cortisol, and adiponectin), milk volume assessed by 48-h test-weighing, and maternal engagement with the infant. Infant behaviour, including crying and sleeping, and infant appetite will be evaluated. Data about other mediators such as maternal perception of milk supply and salivary oxytocin will be collected.

**Discussion:**

We hypothesise that the use of the breastfeeding meditation will reduce maternal stress and consequently improve infant growth mediated by changes in milk composition and volume and maternal behaviour. This study will allow us to understand the mother–infant factors that influence breastfeeding in late preterm infants and potentially identify a method that could improve mother, infant, and breastfeeding outcomes.

**Trial registration:**

ClinicalTrials.gov, NCT03791749. Registered 1 January 2019.

## Background

Nutrition during infancy has the potential to offer short- and long-term benefits through ‘programming’ during this critical window of growth [1]. Breast milk is an unparalleled source of nutrition that can also provide protective benefits for lactating mothers [2]. However, the percentage of women meeting the recommendations for breastfeeding duration, set forth by the World Health Organisation, is below target levels. The reasons for this are multiple and include the challenges that women face that hinder breastfeeding success, such as not receiving enough support. Interventions are therefore needed to support breastfeeding mothers to improve maternal, breastfeeding, and infant outcomes.

Breastfeeding also involves signalling between the mother and the offspring [3, 4]. Early-life environmental signals have the capability of modulating the development of the infant, leading to an adult physiology and metabolism, and consequently disease risk, that is influenced by those early-life signals [5]. The mother is the main source of these signals for young animals and, in Eutherian mammals, regulates the growth of her offspring through placental nutrition during gestation and through lactation post-delivery [6]. Maternal nutritional status, disease history, and social status might determine the signals the mother sends to her infant [6, 7]. Impaired maternal psychological state could also be a factor influencing the type of signals the mother is transferring to her infant. This could be in the form of altered production of breast milk and certain constituents of breast milk (macronutrients or hormones) and/or reduced nurturing behaviours (touching, holding, sensitivity to cues). Both these physical and physiological trade-offs may then alter infant development and behaviour accordingly [8]. Therefore, it is important to optimise the signals the mother is sending to her infant.

Other trade-offs between maternal investment and infant development may exist. During pregnancy and the postpartum period, many mothers experience cognitive changes including forgetfulness and poor concentration, colloquially known as ‘baby brain’ [9, 10]. These changes can be attributed to the hormonal changes mothers go through during these periods, namely changes in estradiol, progesterone, prolactin, oxytocin, and cortisol. It was previously shown that cortisol was associated in an inverted U-function with verbal recall scores and spatial abilities and that lower levels of cortisol were correlated with better attention scores [9]. Recently, significant reductions in grey matter involved in social cognition were found from pre- to post-pregnancy in first-time mothers, which might play a role in postnatal caregiving behaviours and to enhanced maternal–infant relationships [11]. Therefore, breastfeeding-associated hormones may influence cognitive function, facilitate adaptive brain restructuring, and improve maternal caregiving behaviours. Similarly, reducing maternal stress and thus cortisol levels might produce similar effects.

Late preterm infants (LPI), defined as infants born from 34 0/7 to 36 6/7 weeks, constitute 74% of all preterm births and are the fastest growing subset of neonates [12]. Compared to term infants, LPI have a significantly higher risk of morbidity, including jaundice, hypoglycaemia, temperature instability, and respiratory distress [13, 14]. The last 6 weeks of gestation represent a critical period for brain development; therefore, LPI may have an increased risk of behavioural and emotional problems and inferior academic performance later in life [15–18].

Breastfeeding difficulties are the leading complication experienced by LPI [19]. They are less likely to be breastfed, which could be due to infant- and maternal-related barriers. Infant barriers include poor muscle tone and neurodevelopmental immaturity, which may interfere with effective sucking patterns and the ability to give hunger cues. LPI are also more likely to experience rapid fatigue during feeding, lower stamina, fewer awake periods, and reduced effort to stimulate and empty the breast, consequently leading to poor milk production and inadequate intake [19–21]. Maternal barriers to breastfeeding may include various factors associated with preterm birth, such as caesarean delivery, obesity, multiple births, or maternal psychological distress [19]. Mothers of LPI may also experience higher levels of anxiety, depression, and stress, each of which is an independent risk factor for breastfeeding failure in this population [22]. Lastly, some of the commonly cited breastfeeding challenges for mothers of LPI include perceived insufficient milk supply and inadequate support by health care providers post-discharge [23, 24].

This is important because premature infants, including LPI, extract the greatest benefit from receiving breast milk [25–28]. Due to their developmental immaturity and increased susceptibility to inflammation, oxidative stress, and infections, breastfeeding and the constituents of breast milk are particularly beneficial for this group [29, 30]. For instance, in a large cohort of 1130 late and moderately preterm infants, not receiving breast milk at hospital discharge was an independent risk factor for moderate/severe cognitive impairment at 2 years of age [31].

Previously, two RCTs used a relaxation tape as a form of relaxation therapy and found that it increased milk production in mothers of preterm infants [32, 33]. These studies have some methodological limitations that ought to be addressed in future RCTs. Firstly, in one study, milk volume at baseline was not measured and milk production was assessed from a single breast expression session at the end of the study. In both studies, it was unclear whether the milk collection procedure was standardised for time of last feed, time of day, or lactational stage; all of which may influence the volume of milk available for expression. Lastly, neither study reported the exclusivity of breastfeeding, which can influence milk yield. Another RCT investigated the use of a guided imagery meditation tape for breastfeeding mothers of healthy term infants in Malaysia [34]. The therapy was effective in reducing maternal stress and increasing infant weight gain and sleep duration. This research showed that relaxation therapy has benefits for mothers and infants that belong to a low-risk group (high socioeconomic status, full-term infant, healthy mother, high family support, practicing traditional confinement period). Therefore, the benefits might be even greater in higher risk groups, such as mothers of premature infants.

This study will examine the psychological, behavioural, anthropological, and physiological aspects of lactation in breastfeeding mothers of LPI. The primary aim is to determine the effect of a relaxation therapy on maternal stress and infant weight gain. Secondary outcomes of the intervention include breast milk composition (macronutrients, human milk oligosaccharides (HMO), ghrelin, leptin, cortisol, adiponectin), breast milk volume, infant appetite and behaviour, maternal engagement, maternal cognitive function, and maternal salivary cortisol and oxytocin. These secondary outcomes will help address the potential mechanisms by which maternal stress could affect infant growth and ascertain whether there are maternal costs as well as infant benefits.

## Methods/design

### Study design

The Mother and late Preterm Lactation Study (MAPLeS) is an RCT using a breastfeeding meditation for breastfeeding mothers of LPI. Participants will be identified from multiple hospitals with the capacity to care for LPI in London, UK. Eligible mothers will be randomly allocated to either the intervention group, where they will be asked to listen to the relaxation therapy, or to the control group where no intervention is given. The first home visit will be conducted at 2–3 weeks post-delivery, when treatment will commence. At this time point, it is likely that LPI would be discharged from the hospital and that breastfeeding would be somewhat established. One of the main aims of the study is to investigate mother–infant signalling through breastfeeding; therefore, it is important to target women who are more likely to be breastfeeding for the duration of the study. The second home visit will be at 6–8 weeks post-delivery for follow-up. At both time points, questionnaires, breast milk and saliva samples, and anthropometric measurements will be collected. We will also follow-up at 3 and 6 months post-delivery by email or phone to assess breastfeeding status. The SPIRIT figure and study design flow chart are shown in Figs.1 and 2.

**Fig. 1 Fig1:**
[figure not shown]
Standard Protocol Items: Recommendations for Interventional Trials (SPIRIT) figure; schedule of enrolment, interventions, and assessments. ^1^Breast milk samples will be collected in a standardised procedure and will be analysed for macronutrient, human milk oligosaccharide, ghrelin, leptin, adiponectin, and cortisol content

**Fig. 2 Fig2:**
[figure not shown]
Study flow chart. *Intervention group only

### Hypotheses

#### Primary hypotheses

Mothers in the intervention group, using the relaxation therapy from week 2–3 post-delivery, will have a higher reduction in maternal stress score (*primary maternal outcome*) by week 6–8 post-delivery compared to mothers in the control group.Infants in the intervention group will have a higher gain in weight Z-score (*primary infant outcome*) by week 6–8 post-delivery compared to infants in the control group.

#### Secondary hypotheses

The use of relaxation therapy at week 2 post-delivery will result by 6–8 weeks post-delivery in:
Increased fat and energy content of breast milkHigher concentration of HMOs, ghrelin, leptin, and adiponectin in breast milk and lower cortisolIncreased milk volumeHigher concentration of salivary oxytocinReduced time spent crying and increased duration of sleep by the infantHigher prevalence of exclusive breastfeedingBetter verbal memory scoresGhrelin, leptin, and adiponectin concentrations in breast milk are associated with:
Infant behaviour (time spent crying and duration of sleep) and appetite traitsInfant weight Z-scoreMaternal BMI, pregnancy weight gain, and pre-pregnancy BMI

### Participants

Breastfeeding mothers of LPI will be eligible to participate in this study. The specific inclusion and exclusion criteria are detailed in Table 1.

**Table 1 Tab1:** Inclusion and exclusion criteria

Screening	Inclusion Criteria	Exclusion Criteria
Primary Screening	Infant born late preterm (34–37 weeks) & medically stable	Infant born < 34 weeks or > 37 weeks and/or requires hospitalisation for more than 2 weeks
	Singleton pregnancy	Multiple pregnancy
At Recruitment	Intending to breastfeed for at least 6 weeks	Intending to breastfeed for less than 6 weeks
	Mother and infant free of serious illness that may impact breastfeeding	Mother and/or infant have serious illness that interferes with breastfeeding
	Speaks and understands English	Does not understand or speak English
	Non-smoker	Mother currently smoking or intending to smoke while breastfeeding
	Based in London	Not based in London
	Mothers with no prior breast surgery	Mothers with prior breast surgery that affects breastfeeding
Secondary Screening At Phone Follow Up	Interested in participating further	Not interested or unable to participate further
	Still intending to breastfeed for at least 6 weeks	Intending to breastfeed for less than 6 weeks
	Breastfeeding at 2 weeks	Only providing formula

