#### Randomisation and blinding

After the first home visit, each mother will be randomly allocated to either the intervention group (relaxation therapy) or control group. Randomisation assignments will be prepared by a member of the research team, who will have no contact with the mothers, using a computer-generated list stratified for gestational age and parity. Assignments will be stored in sealed opaque envelopes. The assignment will be revealed 3 days after the first home visit when the researcher will retrieve the infant weighing scale from the participant and provide mothers in the intervention group with the meditation tape and meditation use log. To avoid contamination between the intervention and control group, mothers will not be informed about this process until the end of the study, when they will all be offered the meditation.

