### Statistical analysis

Data will be entered and analysed on SPSS v23.0. Kolmogorov-Smirnov test will be used and histograms and Q-Q plots will be assessed to test for normality. Results will be considered statistically significant at *p* < 0.05. The main analysis of the randomised controlled trial results will be an intention-to-treat analysis, but we will also be looking at whether there is a ‘dose–response’ effect between the use of the audio and the outcomes. For the primary outcomes, the differences in weight Z-score and PSS score between groups will be analysed using independent sample *t*-test, taking into account the baseline weight and stress scores (Supplementary Table 1). Similarly, for the secondary outcomes, differences between control and intervention in milk composition, milk supply, maternal cognitive function, maternal salivary cortisol/oxytocin, EPDS score, mother–infant attachment, and infant behaviour will be analysed using independent sample *t*-test. As a secondary analysis, the relationship between breast milk hormones and infant behaviour, growth and sex and maternal anthropometric measures will be analysed using univariate regression, while adjusting for confounding factors such as randomisation status, gestational age, and bottles of formula fed in the previous 7 days (Supplementary Table 1).

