## Discussion

This study will allow us to observe causal relationships between maternal stress and infant growth and to investigate potential mediators between the two including breast milk composition and volume, maternal engagement, and infant behaviour. We will also examine whether reducing maternal stress levels, and thus maternal costs, could help improve both cognitive function and caregiving behaviours.

While the gold standard for estimating milk intake is the ‘dose-to-mother’ stable isotope technique, it will not be possible to use it with this sample. Mothers of LPI are likely to be expressing milk, to increase their supply or to provide top ups. They might also be providing formula top ups. In this trial, therefore, we will be asking the mothers to test-weigh their infants for 48 h and to log the amount of expressed breast milk or formula consumed at each feed.

If proven beneficial, the study will be able to highlight a simple accessible method to improve breastfeeding outcomes in a vulnerable population. It will also provide insight on mechanisms by which maternal stress can influence breastfeeding success and infant development and help in understanding how to optimise late preterm infant growth. We will also be able to identify some of the barriers and facilitators of breastfeeding a LPI.

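### Mixed feeders are admitted, but no visible milk-volume or weight comparison uses baseline feeding mode, an avoidable loss of precision in a trial of 34 to 40 mothers per arm

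*Protocol article*

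**What the plan says.** **Entry.** In Table 1 of the protocol article (Participants), the secondary screen requires "Breastfeeding at 2 weeks" and excludes mothers "Only providing formula". No minimum share of breast milk is set. The Discussion says of these mothers: "They might also be providing formula top ups".

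**Allocation.** Randomisation and blinding describes a "computer-generated list stratified for gestational age and parity". Feeding mode is not a factor.

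**Analysis.** Under Statistical analysis, the two primary outcomes are compared by "independent sample *t*-test, taking into account the baseline weight and stress scores (Supplementary Table 1"). The secondary outcomes, milk supply among them, follow with the linking word 'Similarly' and a t-test, with no covariate named. The phrase "bottles of formula fed in the previous 7 days" appears once, as an adjustment in the secondary regressions relating milk hormones to infant and maternal measures. No analysis is stated there for the prevalence of exclusive breastfeeding, although it is a secondary hypothesis.

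**The protocol's own view of the variable.** The Background remarks of two earlier relaxation trials that "neither study reported the exclusivity of breastfeeding, which can influence milk yield".

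**What is collected before assignment is revealed.** The first home visit leaves a Breastfeeding Status Questionnaire to be filled in over the next three days and starts 48 h of test-weighing. According to the Discussion, expressed milk and formula are logged at each feed. Assignment is revealed three days after the visit, when the scale is retrieved.

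**The concern.** The protocol treats feeding exclusivity as prognostic for milk yield, and treats formula use as a confounder in its hormone regressions. It collects the variable before assignment is known. Yet the visible text does not use it in the randomised comparisons that depend most directly on feeding mode: milk volume, exclusive breastfeeding, and infant weight Z-score, which is a primary outcome.

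With 34 to 40 mothers per arm, the arms can differ noticeably by chance in the share who mix-feed. An unadjusted comparison carries that difference into the estimate and pays for it with a wider interval. At stake is the precision of the milk-volume result, which is one of the trial's proposed mechanisms, and to a lesser degree the power for the primary infant outcome.

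**Working it through.** **1. The plan's own sample size reproduces.** With F = (1.96 + 0.8416)² = 7.849 and N = 2Fσ²/d² per group:
- Stress score (σ = 4.4, d = 3): 2 × 7.849 × 19.36 / 9 = 33.77, so 34.
- Weight Z-score (σ = 0.8, d = 0.55): 2 × 7.849 × 0.64 / 0.3025 = 33.21, so 34.

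The total is 68, and 68/0.85 = 80 is the recruitment target. Nothing below changes these figures.

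**2. Chance imbalance in feeding mode.** The documents do not give the share of exclusive breastfeeders, so a range is assumed. At 50%, the SD of the between-arm difference is √(2 × 0.25/34) = 0.121, with a 95% range of ±0.238. With 40 per arm the figures are 0.112 and ±0.219. Exact binomial probabilities with 34 per arm:

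| Share exclusive (assumed) | Difference of at least 10 points | Difference of at least 20 points |
|---|---|---|
| 30% or 70% | 35.4% | 8.5% |
| 50% | 39.6% | 11.4% |

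**3. Milk volume.** Assumptions: half mix-feed, the SD within each feeding group is 150 ml/day, and exclusive and mixed feeders differ by Δ = 150 or 300 ml/day.
- Total SD = √(150² + 0.25Δ²) = 167.7 or 212.1. Feeding mode explains 0.25Δ²/(total SD)² = 20% or 50% of the variance.
- Unadjusted 95% half-width = 1.96 × total SD × √(2/34) = ±79.7 or ±100.8 ml/day.
- Adjusted half-width = 1.96 × 150 × √(2/34) = ±71.3 ml/day, ignoring the lost degree of freedom. The reduction is 11% or 29%.
- The part due to imbalance is 0.238 × Δ = ±36 or ±71 ml/day. It lies inside the unadjusted interval: 35.7² + 71.3² ≈ 79.7², and 71.3² + 71.3² ≈ 100.8².

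**4. Weight Z-score.** If exclusive and mixed feeders differ by g = 0.2 to 0.6 Z (assumed), a 20-point imbalance moves the group difference by 0.2g = 0.04 to 0.12 Z, which is 7% to 22% of the 0.55 target. For power with 34 per arm, the residual SD is 0.8√(1 − R²):

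| R² from feeding mode (assumed) | Power for 0.55 Z |
|---|---|
| 0 | 0.81 |
| 0.05 | 0.83 |
| 0.10 | 0.85 |
| 0.20 | 0.89 |
| 0.30 | 0.92 |

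At an even split, R² = 0.25g²/0.64, so g = 0.2 to 0.6 corresponds to R² of only 0.016 to 0.141, and R² = 0.30 would need a gap of about 0.88 Z. The lower rows are therefore the more plausible. Part of this gain may already come from the planned use of baseline weight.

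**The case against.** **The covariates may be specified elsewhere.** Statistical analysis refers to Supplementary Table 1 for both the primary comparisons and the regressions, and that table is not shown. The regression confounders are introduced as examples. An article condenses its protocol, and a fuller covariate list may sit in the analysis plan. This stands as a limit: the point concerns the method as visible, and omission from the full plan cannot be asserted.

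**Baseline adjustment may already reach milk volume.** The word 'Similarly' could carry it over from the primary outcomes. First-visit milk volume is the same quantity measured earlier and would probably absorb much of what a feeding-mode flag carries. This is a fair reading, but the text does not say so, and baseline milk volume is not stated to enter the weight or exclusive-breastfeeding comparisons.

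**There is no bias.** Randomisation balances feeding mode in expectation, and the t-test's standard error already includes chance imbalance, so the 5% error rate holds. This stands in full. A reader might take the ±36 to ±71 ml/day as error on top of the reported interval; step 3 shows that it is a component of that interval.

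**The trial does not repeat the fault it criticises.** A reader might infer that it does. But the Background faults the earlier trials for not reporting exclusivity. This trial records feeding status at both visits, logs formula at each feed and makes exclusive breastfeeding a secondary hypothesis. That stronger reading is not supported.

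**Broad entry is reasonable.** It suits a population in which top-ups are expected. Agreed; eligibility is not the fault.

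**Conclusion.** The point holds as a matter of efficiency. Entry is broad in feeding mode, allocation does not balance it, and the visible randomised comparisons of milk volume and weight Z-score do not name it, although the protocol regards it as prognostic and collects it before assignment is revealed. The consequence is a wider interval than necessary and estimates that are sensitive to chance imbalance. It is not systematic bias, an inflated false-positive rate or a shortfall in sample size.

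Under the assumed inputs, the milk-volume half-width could fall by about 11% to 29%. Power for weight Z-score could rise from 0.81 to between 0.83 and 0.92, with the upper end requiring a large gap between feeding groups. All these sizes rest on assumptions about the share of mixed feeders, the gap between feeding groups and the milk-volume SD, none of which the documents give. Nor do the documents support calling feeding mode the strongest predictor of milk volume; first-visit milk volume is likely to be stronger. For exclusive breastfeeding, the visible text states no analysis, so it cannot be said that this outcome is compared without baseline feeding mode.

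**What to change.** State the following before the data are analysed, after checking it against Supplementary Table 1:

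- **Milk volume:** ANCOVA (linear regression) of the 6–8 week 48-h volume on randomised group, with first-visit 48-h test-weighing volume and first-visit feeding mode (exclusive versus any formula in the previous 7 days) as prespecified covariates.
- **Weight Z-score:** add first-visit feeding mode to the baseline-adjusted model.
- **Exclusive breastfeeding:** state the comparison and include first-visit feeding mode. If few mothers who mix-feed at the first visit later become exclusive, a plain logistic model may fail to converge, so name a fallback.
- **Timing:** use only values collected before assignment is revealed. The questionnaire is filled in over the three days after the visit, so the completion date should be checked. Never adjust for the 6–8 week feeding mode or volume, which the intervention may change and which are themselves outcomes.

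Eligibility, stratification, sample size, visits and data collection stay as they are. The cost is a few lines of analysis text and one or two degrees of freedom per model.
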